**Methods::**

This study adopts a mixed- and multi-methods design comparing the effects of the GHI in 42 intervention health facilities (i.e. primary, secondary and tertiary) in the Greater Accra Region versus 56 control health facilities in the Central and Western Regions. The evaluation design is guided by the RE-AIM framework underpinned by the WHO health systems building blocks framework, integrated by the Institute of Medicine’s six dimensions of health care quality: safe, effective, patient-centered, timely, effi cient, equitable. The assessment tools include: (i) a health facility survey, (ii) a healthcare provider survey assessing the knowledge, attitudes, and practices on hypertension and CVD management, (iii) a patient exit survey, (iv) an outpatient and in-patient medical record review and (v) qualitative interviews with patients and various health system stakeholders to understand the barriers and facilitators around the implementation of the GHI. In addition to primary data collection, the study also relies on secondary routine health system data, i.e., the District Health Information Management System to conduct an interrupted time series analysis using monthly counts for relevant hypertension and CVD specific indicators as outcomes. The primary outcome measures are performance of health service delivery indicators, input, process and outcome of care indicators (including screening of hypertension, newly diagnosed hypertension, prescription of guideline directed medical therapy, and satisfaction with service received and acceptability) between the intervention and control facilities. Lastly, an economic evaluation and budget impact analysis is planned to inform the nationwide scale-up of the GHI.

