The medical records of outpatient and inpatient folders at two cross-sectional timepoints before and after GHI implementation are being reviewed to assess between group differences in hypertension and CVD care delivery. Eligibility of medical records are pre-specified based on confirmed diagnosis of hypertension or CVD, and complete medical records with at least data available on patient demographics (age, sex), medical history (confirmed case of hypertension or CVD), laboratory results (any test prescribed, or test reports reviewed), and medical treatment or prescription.

Lastly, DHIMS2 data routinely collected by the MoH in Ghana to monitor service provision consisting of monthly facility-specific counts for a wide range of services, including CVD will be analyzed to assess the differences in care delivery between the intervention and control health facilities over the time period. In line with prior work, to translate monthly counts into indicators that adequately capture service coverage, we construct outcome variables that account for the underlying target population living in the catchment area of a given facility [32]. More specifically, we apply interrupted time series analysis to DHIMS2 data to assess impact on the following CVD indicators: prevalence of hypertension, coronary heart disease, stroke, heart failure and related mortality.

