Next, when analyzing the KAP survey we will report the demographic characteristics of healthcare providers by the intervention and control arm facilities, reporting the mean (standard deviations, SD) or median (25th and 75th percentiles) for continuous variables and frequencies (percentages) for categorical variables. Knowledge about CVD symptoms and modifiable risk factors will be reported as number (percent) by overall and intervention and control arm facilities. Next, each correct response for knowledge related questions will be assigned a score of 1 and the total score for the knowledge of CVD risk factors and treatment recommendations will divided by tertiles and classified as minimal, moderate, and high knowledge. The mean (SD) for knowledge of CVD risk factors and treatment will also be reported by intervention and control facilities. Finally, the correct scores for the knowledge of CVD risk factors and treatment strategies will be classified into high knowledge (> 75% correct responses) and poor knowledge (≤ 75% correct responses) using arbitrary threshold for comparison and also informed by the published literature [35] [36]. The chi-square test will be performed to investigate the difference in knowledge scores between intervention and control arm facilities across age-group, sex, and education strata. Bivariable and multivariable regression analyses will be performed to assess the factors associated with high knowledge of CVD symptoms, and modifiable risk factors. The unadjusted and adjusted odds ratio with 95% confidence intervals (CI) will be reported. The model will be adjusted for age, sex, type of health facility and type of healthcare worker.

Lastly, an interrupted time-series analyses (ITSA) is carried out to establish effects of the GHI on the screening, diagnosis, and management of hypertension / CVD, if aggregate facility-level monthly data are available from the DHIMS2. ITSAs apply segmented regression to assess the impact of events that have occurred at a clearly defined point in time. Data points recorded in the GHI enabled DHIMS2 system will be analyzed by month to examine trends over time and seasonality. We will also evaluate change in patient outcomes over time (e.g., mean systolic BP change).

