**Figure 4 F4:**
[figure not shown]
Summary of the evaluation components, tools and outcomes measures *Fidelity and Acceptability were only assessed in the interventional health facilities. KAP = Knowledge, attitude and practice.

**Table 1 T1:** Health service delivery evaluation: domains, indicators, and tools.

Domains	Process Indicators	Outcome Indicators	Sustainability Indicators
Safety	No. and proportion of sites having access to guidelines, equipment; Type of out-patient and emergency services available by facilities.	Annual death rate for CVD; Incidence of CVD; Prevalence of hypertension; Prevalence of CVD	Workforce appropriate (workforce adequate in volume and distribution); Equipment adequate.
Tools	Health facility survey; Key informant Interviews	Health facility survey; DHIMS2 dataset	Health facility survey; Key informant Interviews
Timeliness	Annual hypertension screening coverage; CVD preventive and treatment services offered.	Total waiting time for physician consultations; Total in-person consultation time; Treatment received within 24 hours of CVD admission.	Workforce sustainability (staff retention per year, staff stability per year).
Tools	Health faclity survey	Health facility survey	Key informant interviews
Effectiveness	No. of HTN patients seen; No. of CHD patients seen; No. of stroke patients seen; No. of heart failure patients seen; No. of hospitalizations by CVD conditions; Average length of hospital stays (in days); No. of acute emergency transfers related to CVD; No. of referrals to higher facilities for CVD; No. of referrals to lower health facilities for CVD.	No. and proportion of patient diagnosed with hypertension; Number and proportion of patients diagnosed with CVD; Number and proportion of CVD patients prescribed evidence-based medicines; Number and proportion of patients with BP < 140/90; Number and proportion of patients with LDLc< 100 and < 70 in those with CVD; Number and proportion of patients who do not smoke.	Linkages - referral pathways (coordination of care across providers, specialist access); No of referrals per year; No of specialist consultations per year.
Tools	Health facility survey	Health facility survey; DHIMS2 dataset; Patient exit survey	Health faclity survey; Key informant interviews
Patient centered care	No. of follow-up appointments.	Treatment satisfaction; Proportion of patients in regular follow-up.	Infrastructure (IT-internet access, equipment access, staff availability or shortage)

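### The DHIMS2 interrupted time series names disease prevalence as its outcome, but the catchment-adjusted monthly service counts behind it measure service use or detection

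*Protocol article*

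**What the plan says.** In the section Data collection Tools, Indicators, and Strategies, the article describes DHIMS2 as routine data "consisting of monthly facility-specific counts for a wide range of services, including CVD". The stated aim of the step that turns these into outcomes is "to translate monthly counts into indicators that adequately capture service coverage". The method given for it is an adjustment for population: "we construct outcome variables that account for the underlying target population living in the catchment area of a given facility". The next sentence is presented as the specific version of that plan. It says the interrupted time series will "assess impact on the following CVD indicators: prevalence of hypertension, coronary heart disease, stroke, heart failure and related mortality".

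Table 1 repeats the label. Among the outcome indicators of the Safety domain it lists "Prevalence of hypertension; Prevalence of CVD", and the DHIMS2 dataset is one of the two tools named for that cell, beside the health facility survey.

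Two other places describe the same analysis differently. The Statistical analysis section says it is to establish "effects of the GHI on the screening, diagnosis, and management of hypertension / CVD". The Methods paragraph of the abstract describes it as "using monthly counts for relevant hypertension and CVD specific indicators as outcomes". Neither mentions prevalence.

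Table 1 also makes continuity of care something to be evaluated. Under patient-centred care, the number of follow-up appointments is a process indicator and "Proportion of patients in regular follow-up" is an outcome indicator.

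The article does not say whether one DHIMS2 count is a visit, a person or a newly diagnosed case, or how repeat attendances are handled.

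**The concern.** Prevalence is the share of a population that has a condition at a given time, whether or not those people come to a clinic. A monthly facility count, however it is scaled to the catchment, contains only people who came and were recorded. It therefore rises when more cases are found or more patients stay in care. If repeat attendances are counted, it also rises when the same patients come more often.

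Those are changes the GHI is meant to bring about or the evaluation assesses. A level or slope change after the start of the programme could be a sign of success, yet under the named outcome it would be reported as an increase in hypertension, coronary heart disease, stroke or heart failure. Lengthening the interval between visits could look like falling disease. The catchment adjustment works on the population side of the ratio and does nothing about what a unit in the count represents.

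**Working it through.** The article gives no sample size, power or effect size for the interrupted time series, so there is no planned figure to reproduce. The check has two parts: what each possible counting unit would measure, and how far a visit-based indicator could move with disease held constant.

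**Part 1. What the ratio measures under each counting unit**

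| Unit of the monthly count | What the catchment-adjusted figure is | Does visit frequency move it? | Is it population prevalence? |
|---|---|---|---|
| Visit | Contacts per resident per month | Yes | No |
| Person attending in the month | Monthly attendance rate | Yes, when visit intervals are a month or longer | No |
| Newly diagnosed case | Detection rate | No | No |

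A count of patients on a facility register would also be free of repeat visits. It would still give the share known to the facility, which moves with detection and retention. The DHIMS2 description does not mention such a count.

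**Part 2. Illustration for hypertension**

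Inputs from the Background section: prevalence 38%, treatment 32%. Assumptions made here:
- The 32% is a share of all people with hypertension.
- Only treated patients attend.
- Visits are spread evenly over months.
- Adjustment means simple division by the catchment population.
- The visit intervals are as shown below.

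Per 10,000 residents (an arbitrary size that cancels out), 10,000 × 0.38 = 3,800 have hypertension and 3,800 × 0.32 = 1,216 are in care.

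Monthly indicator = 0.38 × 0.32 / (visit interval in months):
- every 6 months: 0.1216 / 6 = 2.0%
- every 3 months: 0.1216 / 3 = 4.1%
- every 2 months: 0.1216 / 2 = 6.1%
- every month: 0.1216 / 1 = 12.2%

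The true prevalence is 38% throughout. The gap between these values and 38% combines two things, people not in care and visit spacing, so it should not be read as the effect of repeat counting. The change between intervals isolates that effect: from 3-monthly to 2-monthly visits, 6.08 / 4.05 = 1.50, or +50% with no new case. This ratio is 3/2 and does not depend on the 38% or the 32%. If the 32% instead applies only to the 34% who are aware, 0.38 × 0.34 × 0.32 = 0.0413. That gives 1.4% at 3 months and 2.1% at 2 months, again +50%.

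Counting each person once within a month does not remove the effect when intervals are a month or longer. It only caps the value: at two visits a month, raw visits give 2 × 12.16 = 24.3% and distinct attenders give 12.2%.

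More patients in care also moves the figure. With the interval held at 3 months, raising the share in care from 32% to 40% gives 0.38 × 0.40 / 3 = 5.1%, and to 50% gives 0.38 × 0.50 / 3 = 6.3%, against 4.1% at 32%. Prevalence is again unchanged.

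**The case against.** The strongest reply is that the article never says a patient is counted at every visit, nor that counts are simply divided by population. It refers to prior work for the construction, and field definitions could properly sit there or in a fuller document. If the fields hold new cases only, visit frequency has no effect and the 50% disappears. This stands. A reader might infer that repeat counting is an established feature of the plan, but the documents do not support that, and their silence on the counting unit is not itself the defect. The defect is a positive statement: prevalence is named as the outcome, and none of the units considered above yields it.

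A second reply is that the surrounding text already frames the analysis as care delivery and service coverage, so the word is only loose. That is fair as to intent. But the label sits in the sentence that lists the outcomes and is repeated in Table 1, so it is what would be carried into reporting.

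Third, the analysis compares intervention with control facilities, so a change in visit intervals common to both would not by itself appear as a GHI effect. This also stands. A change produced by the GHI would occur in the intervention facilities only, and the comparison would not remove it.

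Fourth, prevalence is not among the listed primary outcomes, and the time series depends on data being available. That limits the weight of the point but does not remove it.

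Finally, a reader might extend the repeat-visit argument to every indicator in the list. It does not reach related mortality, since a death occurs once. It also fits chronic outpatient conditions best.

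**Conclusion.** The point holds as a mismatch between the named outcome and the data. The DHIMS2 outcomes called prevalence are catchment-adjusted service counts. They measure utilisation or detection under a visit, monthly-attender or new-case definition. They also disagree with the Statistical analysis section, which names screening, diagnosis and management as the target.

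The narrower claim, that a change in follow-up frequency induced by the GHI would appear as a change in prevalence, is conditional on repeat attendances being counted. Its illustrated size, +50% for a move from 3-monthly to 2-monthly visits, rests on assumed intervals and is not an estimate of bias in this study.

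The change should be made, because the plan as written could report better detection or retention as a growing disease burden.

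**What to change.** - In Data collection Tools, Indicators, and Strategies, and for the DHIMS2-derived entries in Table 1, replace prevalence with catchment-adjusted service-contact rates, or with new-diagnosis rates where DHIMS2 separates new cases. Model new cases wherever that field exists. The mortality indicator needs no change on this ground.
- State what one DHIMS2 count represents for each indicator: a visit, a person attending in the month, or a new case.
- Bring these places into line with the Statistical analysis section, and say there that a rise in these rates is read as service use or detection and not as disease prevalence.
- Where available, show Table 1's number of follow-up appointments, from the health facility survey, beside any contact-rate result. It is descriptive context and will not fully separate visit frequency from patient numbers month by month. The medical record review should not be relied on for this, because its stated minimum content covers demographics, history, laboratory results and treatment, and does not list visits per patient.

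The cost is mainly wording, plus one descriptive display from a tool already planned. The small downside is that the study no longer claims an effect on prevalence from routine data.

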### Study outcomes

The primary outcome measures being assessed between the intervention and control facilities are: i) proportion of screened individuals for hypertension, ii) newly diagnosed patients with hypertension or CVD, iii) prescription of guideline directed medical therapy for hypertension and CVD, iv) BP control defined as < 140/90 mmHg, v) provider knowledge and practice related to hypertension and CVD and vi) patient centered care and satisfaction. The study also assesses several secondary outcome measures including difference in total waiting time for physician consultation and physician acceptability of the GHI.

### Sample size

The sample size of 1,200 participants in total for the MRR or patient exit survey will provide 90% power to detect 10% relative difference between the intervention and control facilities in processes of care indicators such as prescription of evidence-based therapies and blood pressure control. at an α = 0.05 and accounting for 20% non-response rate or missing data.

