## Background

Cardiovascular diseases (CVD) are the leading cause of death globally, with a disproportionately higher burden (> 80% age-standardized CVD deaths) in low-and middle-income countries (LMICs) [1]. Arterial hypertension, also called high blood pressure (BP), is a leading modifiable risk factor associated with CVD death and disability [2]. While the average age-standardized BP is declining in most high-income countries, it is increasing in LMICs with 32%−50% of adults estimated to have high BP in sub-Saharan Africa (SSA) [3]. Multiple studies have shown that the key drivers of CVD in LMICs include insuffi cient physical activity, low fruit intake, high consumption of processed meat and sedentary lifestyles associated with rising urbanization as well as rising prevalence of hypertension, diabetes, obesity, and smoking [4] [5]. Although hypertension is a largely controllable condition, its actual rates of awareness, treatment, and control are disappointingly low in SSA. Ghana is a lower middle-income country in SSA with an estimated hypertension prevalence of 38%, and sub-optimal hypertension awareness (34%), treatment (32%) and control rate (2%−12%) [6] [7] [8]. A 5-year review of autopsy cases (January, 2006 to December, 2010) at Korle Bu Teaching Hospital, the largest and leading supra-tertiary level national referral and teaching hospital in Accra has attributed 22.2% of all deaths to CVD [9]. In addition to the disease burden, CVD threatens to impose a significant economic burden in Ghana, with more than 40–50% of households paying out-of-pocket for health services and medications [10]. Although there is a National Health Insurance Scheme, it has traditionally covered outpatient visits to improve access for many people, with recent expansion to inpatient care coverage although some services at tertiary level hospitals are not included in the benefit package. Additionally, there are delays in reimbursement of claims to facilities that affect the health system’s ability to provide timely management of hypertension and CVD [11].

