### Statistical analysis

Quantitative data is analyzed by descriptive statistics for demographic, socio-economic and other patient-, provider- and health system level factors between the intervention and control facilities. Differences in service delivery indicators, process of care measures (prescription of guideline directed medical therapy) and clinical outcomes (BP control) will be compared between the intervention and control facilities. The chi-square test is used to evaluate differences between categorical variables. Two-sided p-values < 0.05 will be considered statistically significant. Composite performance scores are defined by determining the proportion of patients who receive concordant care compared to patients who receive discordant care between the intervention and control facilities. Linear and logistic regression analysis techniques are used to assess determinants of health outcomes, processes of care measures, and treatment satisfaction [33]. Random-effects regression analyses will be used to account for cluster effects and imbalances between intervention and control group health facilities; Effect sizes will be presented as risk ratios for binary outcomes, and as mean differences for continuous outcomes; 95% confidence intervals (CI) will be given for both. Missing data in outcome measures will be handled by appropriate imputation methods.

A propensity score will also be created using logistic regression and will contain those variables associated with treatment at a health facility [34]. Analysis of clinical outcomes analysis will also use ANCOVA (analysis of covariance) to compare the prescription of evidence-based medicines, and mean change in BP and lipids between the intervention and control arm facilities [29]. Other outcome measures such as behavioural and biochemical risk factors will be analyzed using logistic or conditional logistic regression to adjust the comparisons for other variables. We shall also compare the percentages achieving clinical and behavioural targets between the intervention and control arm facilities.

The fidelity analysis will uncover the extent to which the GHI was fully or partially implemented by various health system stakeholders.

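### The stated 90% power for a 10% relative difference with 1,200 participants fails for BP control at the document's own rates and cannot be confirmed for prescription

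*Protocol article*

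**What the plan says.** The whole justification is one sentence in the Sample size section. "The sample size of 1,200 participants in total for the MRR or patient exit survey", it states, "will provide 90% power to detect 10% relative difference between the intervention and control facilities in processes of care indicators", with examples given as "such as prescription of evidence-based therapies and blood pressure control", "at an α = 0.05 and accounting for 20% non-response rate or missing data". The Study outcomes section lists both indicators as primary and defines BP control as below 140/90 mmHg. The Statistical analysis section makes testing two-sided.

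The sentence states no control-group proportion. The Background gives the only related rates in the article, national figures described as "sub-optimal hypertension awareness (34%), treatment (32%) and control rate"; the control rate there is 2% to 12%. The abstract compares "42 intervention health facilities (i.e. primary, secondary and tertiary) in the Greater Accra Region versus 56 control health facilities". The Statistical analysis section adds: "Random-effects regression analyses will be used to account for cluster effects". The only allowance named in the Sample size section is 20% for non-response or missing data.

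**The concern.** The number needed for a relative difference depends heavily on the starting proportion. Ten percent of a rate near 80% is 8 percentage points; ten percent of a 12% rate is 1.2 points. One sample size cannot give 90% power for both. The article presents BP control in Ghana as very low, yet states the same 90% power for it as for prescription.

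If the power for a primary outcome is far below the stated value, a non-significant BP-control result could be taken as evidence of no effect from a well-powered evaluation, and the evaluation is meant to inform national scale-up. The planned 95% confidence intervals would show the imprecision, but the stated 90% would still mislead anyone who relies on it.

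**Working it through.** **Inputs.** N = 1,200, 20% loss, 90% power, α = 0.05, 10% relative (Sample size); two-sided (Statistical analysis); control rate 2% to 12%, treatment 32%, awareness 34% (Background); 42 + 56 = 98 facilities (abstract). Assumed, because not stated: a 1:1 split of participants, and any ICC.

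**Formula.** Two-proportion normal approximation with n per arm, p2 = 1.1 × p1 and p̄ the mean of p1 and p2:

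z = [(p2 − p1) − 1.96 × √(2p̄(1 − p̄)/n)] / √([p1(1 − p1) + p2(1 − p2)]/n), power = Φ(z).

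Evaluable: 1,200 × 0.8 = 960, so n = 480.

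**Can the plan's figure be reproduced?** Yes, at suitable baselines without clustering:
- 10% relative from 79% (to 86.9%): 950 evaluable, 950/0.8 = 1,188.
- 10 percentage points, 32% to 42%: 976 evaluable, 976/0.8 = 1,220.
- 10 percentage points, 60% to 70% (30% to 40% is the mirror image): 954 evaluable, 954/0.8 = 1,193.

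**BP control, relative reading.** At p1 = 0.12, p2 = 0.132: z = (0.012 − 1.96 × 0.02142)/0.02142 = −1.40, power 8%.

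| Control proportion | Source | Power, n = 480 per arm |
|---|---|---|
| 2% | Background, lower end | 4% |
| 12% | Background, upper end | 8% |
| 35% | 12/34, controlled among aware (assumption) | 20% |
| 37.5% | 12/32, controlled among treated (assumption) | 22% |

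These count rejections in the favourable direction only; counting both directions gives 5.5% at 2% and 8.7% at 12%. With all 1,200 evaluable (600 per arm), power is 9% at 12% and 26% at 37.5%. For 90% power, 12% to 13.2% needs 32,140 evaluable (40,175 with loss); 2% to 2.2% needs 216,018 (270,023 with loss).

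**Where 90% is reached.** The control proportion must be about 79% with 960 evaluable, or about 76% with 1,200.

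**Prescription, relative reading.** No baseline is given, so power is shown over a range:

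| Control proportion | Power, n = 480 per arm |
|---|---|
| 32% | 18% |
| 50% | 34% |
| 60% | 49% |
| 70% | 69% |
| 80% | 92% |

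**Other variants.** A 42:56 split changes power by about 1 point or less. One-sided testing gives at most 33% at the Background rates. Reading 1,200 as per arm gives 38% at 32%.

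**Clustering (illustration; the article gives no ICC).** Equal yield assumed: 960/98 = 9.8 patients per facility. Design effect at ICC 0.05: 1 + (9.8 − 1) × 0.05 = 1.44; 480/1.44 = 333 effective per arm. At an 80% baseline, power falls from 92% to 90% (ICC 0.01), 81% (0.05) or 70% (0.10).

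**Percentage-point reading.** For 32% to 42% with 960 evaluable, power is 89.5% without clustering, 87% at ICC 0.01, 76% at 0.05 and 65% at 0.10. For 12% to 22% it is 98.6% without clustering and 93% at ICC 0.05.

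**The case against.** The strongest reply is that the Background rates are national figures, not design assumptions. Patients in the record review and exit survey already have a physician diagnosis, and an eligible folder must hold treatment or prescription data. If the 34% awareness and 32% treatment share a denominator, treatment among aware patients is 32/34 = 94%, above the 79% threshold. This stands for prescription: a reader might infer that the claim fails there too, but the article gives no prescription rate, so it does not show that. The 94% does not confirm the claim either, because a 10% relative increase from it exceeds 100% (0.94 × 1.1 = 1.034). For BP control the reply fails, since re-expressing 12% among aware or treated patients still gives only 20% to 22% power.

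Three stronger readings are also tempting.

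- *That the word relative is a slip for percentage points.* Ten points from 32% gives 1,220, but 1,193 and 1,188 fit 1,200 at least as well, and the last is a relative difference. The match does not identify the source.
- *That clustering was ignored.* The article condenses a fuller protocol that may hold an ICC, and the analysis does plan random effects. What stands is that the published sentence names only the 20% loss and that any design effect above 1 lowers power. The ICC values used here are assumptions.
- *That a before-and-after contrast is grossly underpowered.* Records are reviewed "at two cross-sectional timepoints before and after GHI implementation", but the power statement concerns intervention against control facilities, and difference-in-differences is only hoped for. A power figure for that contrast would test a claim the section does not make.

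**Conclusion.** Wrong as written for BP control. At the article's own 2% to 12%, power is about 4% to 8% against the stated 90%, and about 20% to 22% on the more generous denominators. The claim would need about 79% of control-facility patients to be controlled, which does not fit the Background's account. This rests on 960 evaluable, a 1:1 split, two-sided 0.05 and independent patients; no variant tried at these rates restores 90%.

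For prescription the claim is unconfirmed rather than refuted: it holds without clustering from a baseline of about 79% and fails below that. Whether the 10% is relative or in percentage points decides the BP-control conclusion, because a 10-point difference from 12% would exceed 90% power even at an assumed ICC of 0.05. The article must therefore say which is meant.

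**What to change.** Rewrite the Sample size paragraph to give:

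1. the control-group proportion assumed for each named indicator, and its source;
2. whether the 10% is relative or in percentage points;
3. a design effect with its assumed ICC for the 42 and 56 facilities, and the split of participants between arms;
4. the power, or the difference detectable with 90% power, that 1,200 gives for BP control and for prescription separately.

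As a guide to item 4, at a 12% BP-control rate and ICC 0.05 (both assumptions to be replaced by the authors' own), the detectable relative difference is about 78%, or 0.12 × 0.78 = 9.4 percentage points.

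The cost is one paragraph. Enrolment and analysis do not change; on the relative reading, the stated power for BP control becomes much less favourable.
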